#### Premature discontinuation of study

The trial may be prematurely discontinued by the Sponsor, Chief Investigator or Regulatory Authority on the basis of new safety information or for other reasons given by the DSMB, regulatory authority or ethics committee concerned. The Sponsor and CI reserve the right to stop the trial at any time, for any justifiable reason.

The clinical trial may be prematurely terminated for the following reasons:

Serious and/or persistent non-compliance with trial protocolNon-compliance with ethical standards, regulatory requirements or GCP complianceFindings uncovered during monitoring visits, audits or inspections that compromise patient safety or suitability of the site to act as a trial centreRecommendation from DSMBFailure to meet recruitment targets

The affected trial participants will also be informed promptly and appropriate follow-up visits will be arranged. No further participant data will be collected.

During the course of the study, any of the following events will trigger a halt in patient recruitment and a safety meeting of the DSMB:

Death or life-threatening event occurs due to a reaction to the productOr 2 or more IMP related SAEs of non-lethal non-life-threatening reactions to HMB002.

The trial will be put on hold pending a safety investigation in either case above. If following an internal safety review the sponsor deems it appropriate to restart the trial, this can be done after approval of a substantial amendment.

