#### Trial duration and flowchart

We will aim to recruit the 17 patients (stage 1 and 2) in approximately 36 months. Each individual patient will be intensively followed up for 52 weeks after receiving HMB002 infusion and then for long-term safety monitoring for a further 9 years. The end of the trial will be defined as the last patient 10-year annual follow up post IMP infusion. The duration of the study will also depend on the progression of the study from stage 1 to stage 2. The schedule of assessment has been explained in Fig 1. The trial flow chart is depicted in Fig 2.

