#### Outcomes

*Primary endpoints*.

Safety: Moderate to severe (including life threatening and death) adverse event occurrences due to product in 1^st^ 52 weeks post procedureTolerability: assessed by the proportion of initiated infusions where >80% of the infusion is received by the patient.Biological activity: Survival with native liver at 24 weeks post treatment.

*Secondary endpoints*.

Change in blood marker levels including haematological, biochemical and coagulationbaseline to 52 weeks post treatment.Quality of life measuresPatient survival with native liver at 52 weeks post treatmentPatient survival with transplanted or native liver at 24- and 52-weeks post treatment.

*Exploratory end points*

To assess the assay ‘Hepamorph’ which distinguishes the recipient liver cell derived proteins from the donor liver cell derived proteins using a targeted mass spectrometry approach.To analyse viability and function of microbeads which are retrieved from the intraperitoneal cavity either at laparoscopy or transplant for phenotype ex vivo.

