**Fig 3 pone.0288185.g003:**
[figure not shown]
Participant timeline flowchart.

Safety monitoring will be until 10 years after HMB002 infusion. This will be aligned with routine care. Routine follow up will be conducted annually as a minimum but may be more frequent should the clinical condition of the child or young person require this. For example, if the child has undergone liver transplantation, follow up will be frequent and lifelong.

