#### Statistical methods

*Analysis of primary endpoints*.

The number of moderate to severe adverse event occurrences due to product in 1^st^ 52 weeks post procedure will be reported.The proportion of initiated infusions where >80% of the infusion is received by the patient will be reporter.Survival with native liver at 24 weeks post treatment and 95% confidence interval will be reported as one minus the cumulative incidence of death with native liver, liver transplant being considered as competing events.

*Analysis of secondary endpoints*.

Change in blood marker levels (haematological, biochemical and coagulation) will be reported from baseline to 52 weeks post-treatment.Change in quality-of-life measures levels will be reported from baseline to 52 weeks post treatment.Survival with native liver at 52 weeks post treatment and 95% confidence interval will be reported as one minus the cumulative incidence of death with native liver, liver transplant being considered as competing events.Overall survival and 95% confidence interval at 24 weeks and 52 weeks post treatment will be estimated using the Kaplan-Meier method.

*Other reporting*.

A comprehensive report of the collected examination items will be provided according to the protocol’s schedule of assessment.

An analysis of outcomes will be conducted at stage 1 Go/No Go time point for DSMB safety review, when the 9^th^ patient has completed their 24-week post IMP study follow up.

According to the trial design, a first analysis will be conducted once 9 patients have received the proposed treatment and completed 24 weeks of follow up. If two or fewer survive with the native liver at 24 weeks after treatment then the trial will be stopped at this stage. Once 52-week follow up is completed for all 9 patients, primary and secondary endpoint will be analysed according to the protocol specification. If more than 2 survive with the native liver at 24 weeks after treatment, then recruitment will continue to a total of 17 patients (stage 2). Once 52 week follow up will be completed for all 17 patients having received the treatment, primary and secondary endpoints will be analysed according to the protocol specification.

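### On premature termination the protocol stops all data collection, with no exemption for children already infused, which does not fit the 52-week safety endpoint or the 10-year safety monitoring

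*Protocol article*

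**What the plan says.** Protocol article, Premature discontinuation of study: the sponsor, chief investigator or regulator may end the trial early "on the basis of new safety information or for other reasons given by the DSMB, regulatory authority or ethics committee concerned". Listed reasons also include a DSMB recommendation, several kinds of non-compliance, and poor recruitment. The consequence for participants is "The affected trial participants will also be informed promptly and appropriate follow-up visits will be arranged", followed directly by "No further participant data will be collected". No exception is made for children who have received HMB002.

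Other sections set the follow-up that each infused child should have:
- Outcomes and Statistical methods: the primary safety endpoint counts moderate to severe "adverse event occurrences due to product in 1^st^ 52 weeks post procedure". The primary biological activity endpoint is "Survival with native liver at 24 weeks post treatment".
- Trial duration and flowchart: each patient is "intensively followed up for 52 weeks after receiving HMB002 infusion and then for long-term safety monitoring for a further 9 years".
- Participant timeline (text under Fig 3): "Safety monitoring will be until 10 years after HMB002 infusion". The Sample size section also gives a 10-year safety period.
- Fig 1, note m: beads are usually removed within 4 weeks, and in any case within 24 weeks.
- Statistical methods, on the nine stage 1 patients: "Once 52-week follow up is completed for all 9 patients, primary and secondary endpoint will be analysed according to the protocol specification".

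**The concern.** A trial that is ended because of a safety signal is the one in which later information on exposed children is most wanted. As printed, the rule ends data capture at that moment in children who may still carry the beads and who are still inside the primary safety window. The children will be seen, because visits are arranged, but what is found at those visits does not become trial data.

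At stake are later product-related events, bead-retrieval findings, the 24-week outcome where it is not yet known, and the whole long-term safety record. The effect falls on a contingency. It does not touch the planned conduct, the primary test or the sample size.

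**Working it through.** **Design figures, for reference.** The two-stage rule (stop if 2 or fewer of 9; success if 7 or more of 17) reproduces with exact binomial sums. Type I error is 0.0341 at a rate of 0.20, and power is 0.8057 at 0.50. N = 17 is not in dispute and does not change.

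**The passages side by side.**
1. Safety endpoint: needs data to week 52. The termination rule collects none after the stop.
2. Biological activity endpoint: needs status at week 24. Under the rule it is not collected for a child who has not reached week 24 and has had no deciding event.
3. Long-term safety: 10 years per child, with no condition that the trial continues. Under the rule it is not collected for anyone. Within the recruitment period of about 36 months no child can have completed 10 years, so any stop in that period removes this element for every infused child.
4. Visits: still arranged after termination. So the rule removes the recording, not the contact.

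**How many children are inside each window at a stop.** Input: 17 patients in about 36 months (Trial duration and flowchart). Assumption: uniform accrual. Children still inside a window = accrual rate × window length, once accrual has run at least that long.
- Rate: 17 / 36 = 0.472 per month.
- Short of 52 weeks (12 months): 0.472 × 12 = 5.7.
- Short of 24 weeks (24 / 4.345 = 5.52 months): 0.472 × 5.52 = 2.6.

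The 2.6 is an upper bound for a missing 24-week outcome, because a child who has already died or been transplanted has a determined native-liver status.

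**Range.**
- Stop at the 9th infusion: 5.7 / 9 = 63% short of 52 weeks.
- Stop at the 17th infusion: 5.7 / 17 = 33%.
- Half the accrual rate (0.236 per month): 2.8 short of 52 weeks and 1.3 short of 24 weeks.
- Stop at the DSMB review planned 4 weeks (0.92 months) after the fourth infusion: with one infusion every 36 / 17 = 2.12 months, follow-up is 0.9, 3.0, 5.2 and 7.3 months. None of the four has reached 52 weeks, and three of the four are short of 24 weeks (5.52 months).

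**The case against.** The strongest defence is that the sections giving 52 weeks and 10 years describe a trial that runs its course, while the termination section is a specific provision for an abnormal end. A general plan with an exception need not be a contradiction. That is fair as logic. But the follow-up sections carry no such condition, and the exception gives a worse result for no stated reason.

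Several stronger readings are tempting, and the document does not support them:
- *That the rule conflicts with the stage 1 futility stop.* It does not. That stop is a planned outcome of the design, all nine children have reached 24 weeks by then, and Statistical methods carries them to 52 weeks. The protocol merely leaves unsaid how the two kinds of stop relate.
- *That any serious product reaction ends data collection.* A product-related death or life-threatening event, or two or more other related SAEs, triggers a recruitment halt and a hold pending investigation. The data sentence is attached to termination, not to the hold.
- *That the trial could not quantify the harm that stopped it.* Adverse events are recorded from consent, and the primary safety analysis is a count of events, so the triggering events are already on file. What is lost is what happens afterwards.
- *That most exposed children are lost.* This holds only for early stops, as the range shows. Those children also keep the follow-up they already have.
- *That truncated children are certain to be dropped from the analysis.* Methods for additional analyses discards patients with incomplete data, but does so alongside continued accrual, which presupposes a running trial. The planned survival methods can use censored follow-up. Discarding is a possible compounding effect, not a stated consequence of termination.

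It also stands that bead removal usually comes early, that care and routine notes continue, and that some grounds for termination (ethical, regulatory or GCP failures) may limit what can be collected. The full protocol may contain an exception; the printed sentence gives none.

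**Conclusion.** The point holds in limited form. The printed rule ends participant data collection on premature termination, safety-driven termination included, without exempting infused children. It does not fit the 52-week safety window or the unconditional 10-year monitoring. During steady accrual at the planned rate, about 5.7 infused children would have a truncated 52-week safety record and at most about 2.6 an unknown 24-week outcome. All infused children would lose the remaining long-term safety data. The counts rest on uniform accrual of 17 in 36 months and fall in proportion if accrual is slower. The textual point does not depend on them. It should be corrected, but it changes no sample size or error rate.

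**What to change.** Replace the sentence that ends data collection. Suggested sense: premature termination closes the trial to further enrolment and infusion. Children already infused, with continuing consent and where the ground for termination and the authorities permit, continue 24-week, 52-week and long-term safety data collection, including the recording of bead retrieval. Add that their observed data are reported and are not discarded under the incomplete-data rule in Methods for additional analyses. One clause should also say that the stage 1 futility stop follows Statistical methods and not this section.

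The change concerns data collection only and leaves clinical management as it is. The cost is protocol wording plus data entry from visits that the section already arranges and from monitoring that the Participant timeline section aligns with routine care. Recruitment has yet to begin, so no collected data are affected.

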#### Methods for additional analyses

There are no subgroups to analyse. Calculation of time to death will consider transplantation as a competing risk.

*Methods in analysis to handle protocol non-adherence and missing data*. This is an early phase trial, so that analysis will be conducted per protocol on patients with available data. Patients with incomplete data will therefore be discarded. Patient accrual will be continued until the required number of patients with complete data is reached.

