#### Sample size

Simon’s two-stage design for a one-sample exact test was estimated, assuming a one-year survival rate of 0.20 or less under the null hypothesis, and 0.5 or more under the alternative, with 80% power and 5% type I error rate. A total of 17 patients will be recruited into the study (at the end of stages 1 and 2). 9 patients will be recruited into the study in the first stage. Once 9 patients have completed their 24 weeks visit, the study will stop for futility if only 2 or fewer patients have survived with the native liver. At the end of the second stage, if 7 or more patients out of the 17 enrolled have survived with native liver at 24 weeks post HMB002 treatment, this will demonstrate proof of concept. DSMB approval is required for progression to Stage 2, where the trial will continue to recruit a further 8 patients. this will be extended to 17 patients as part of the Simon two stage design if there is evidence to support continuation. A long-term follow-up period will be used to monitor safety over a 10-year period post investigational medicinal product (IMP) infusion.

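### Discarding treated children with incomplete data and recruiting until enough complete ones exist conflicts with the 17-enrolled decision rule, can select on outcome, and no longer guarantees the 5% type I error

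*Protocol article*

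**What the plan says.** Under Methods for additional analyses, the protocol article makes the analysis per protocol on patients with available data and adds: "Patients with incomplete data will therefore be discarded. Patient accrual will be continued until the required number of patients with complete data is reached". It does not say which data must be present for a child to count as complete.

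The Sample size section is written for fixed numbers: "9 patients will be recruited into the study in the first stage" and "A total of 17 patients will be recruited into the study". Proof of concept is declared if at least seven of the 17 children enrolled are alive with their native liver at 24 weeks. The interim rule is tied to attendance: "Once 9 patients have completed their 24 weeks visit, the study will stop for futility" if two or fewer have survived with the native liver. Statistical methods times the final analysis by treated patients: "Once 52 week follow up will be completed for all 17 patients having received the treatment".

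Replacement of subjects allows replacement both of children who never receive the infusion and of those who do not tolerate the procedure. Outcomes lists tolerability, as the share of started infusions that exceed 80% delivery, among the primary endpoints.

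**The concern.** A Simon rule has its stated error rates when the children counted are a fixed, consecutive series, chosen before anyone knows how they fared. Here a treated child can leave the series because of something seen, or not seen, after treatment, and another child takes the place. The analysed counts stay at 9 and 17, but they become counts of complete cases rather than of children enrolled or treated, and the number treated becomes open-ended.

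If the discarded children tend to be failures, the retained group looks better than the treated group. Passing stage 1 and declaring proof of concept then both become more likely for an ineffective product. The second replacement route also works against the tolerability endpoint: if replaced children leave the analysis, those who tolerated the infusion badly are the ones removed. The final safety tabulation could likewise omit product-related events in discarded children.

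**Working it through.** **Inputs from the Sample size section.** Method: "two-stage design for a one-sample exact test was estimated". Null: "assuming a one-year survival rate of 0.20 or less under the null hypothesis". Alternative and error rates: "0.5 or more under the alternative, with 80% power and 5% type I error rate". Stage 1 has 9 children and stops at two or fewer successes. The total is 17 and success is seven or more. The rates are labelled one-year survival while the decision uses 24-week native-liver survival; I apply 0.20 and 0.50 to the latter, as the decision rule does.

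**Step 1: reproduce the design.** The chance of declaring proof of concept at true rate p is

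S(p) = Σ over x = 3 to 9 of P[Bin(9, p) = x] × P[Bin(8, p) ≥ 7 − x].

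At p = 0.20 the terms for x = 3 to 7 are 0.0099, 0.0134, 0.0082, 0.0023 and 0.0003, and the rest are negligible. So S(0.20) = 0.0341. At p = 0.50, S = 0.806. The stated 5% and 80% are met. A search over all two-stage designs confirms that 17 is the smallest total that meets them.

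**Step 2: discard and replace.** Let f be the share of failures discarded and s the share of successes discarded. The success rate among retained children is

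p′ = p(1 − s) / [p(1 − s) + (1 − p)(1 − f)],

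and the error is S(p′). The article gives no dropout rate, so f and s are assumptions. Example with p = 0.20, f = 0.20, s = 0: p′ = 0.20 / (0.20 + 0.80 × 0.80) = 0.20 / 0.84 = 0.238.

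| Failures lost (f) | Successes lost (s) | p′ | Type I error |
|---|---|---|---|
| 0 | 0 | 0.200 | 3.4% |
| 10% | 10% | 0.200 | 3.4% |
| 20% | 20% | 0.200 | 3.4% |
| 0 | 10% | 0.184 | 2.2% |
| 0 | 20% | 0.167 | 1.3% |
| 10% | 0 | 0.217 | 5.1% |
| 20% | 0 | 0.238 | 7.9% |
| 30% | 0 | 0.263 | 12.2% |
| 20% | 10% | 0.220 | 5.4% |

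With no successes lost, the error passes 5% at about f = 9.4%, which under the null is 0.80 × 9.4% ≈ 7.5% of all children. The chance of passing stage 1 under the null is 26% as designed and 37% with f = 20%, s = 0.

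**Step 3: number treated.** The expected number treated to obtain 17 complete cases is 17 divided by the retained share. At 10% or 20% loss unrelated to outcome this is 17/0.90 ≈ 19 or 17/0.80 ≈ 21, against the stated total of 17.

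**Step 4: the alternative rule.** Keep all infused children and count unknown status as failure. Lost failures then change nothing, and a share s of lost successes lowers the counted rate to p(1 − s). Under the null this is at most 0.20, so the error is at most 3.4% whatever the missingness. Under the alternative, s = 2%, 5% or 10% gives counted rates of 0.490, 0.475 or 0.450 and power of 78.3%, 74.6% or 67.8%.

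**The case against.** A reader might infer that the rule does select on outcome, because a child who dies early never reaches the 24-week visit and so is dropped. The article does not support that as a certainty. Death and transplant are observed outcomes for this endpoint. Trial design says 24 weeks was chosen to capture late deaths, and a stopping rule that counts survivors makes sense only if non-survivors are among the nine. Data collection and management keeps transplanted children in follow-up and seeks permission to use routine data after withdrawal. If deaths and transplants are all counted, unknown status falls mainly on children last seen alive with their native liver. Many of these may be successes, and losing them lowers the error.

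A reader might also infer that the 5% error is invalidated outright. It is not: the design has slack (3.4%), and only preferential loss of failures uses it up. Nor do the planned Kaplan-Meier and cumulative-incidence analyses contradict the rule. They can accommodate partial follow-up, but the reason given for cumulative incidence is that transplant is a competing event, and that remains with complete data.

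On safety, adverse event collection, the halting rules and DSMB review do not depend on completeness, so only the final count is in doubt.

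Finally, this is a condensed article, and a definition of incomplete may sit in the full protocol or analysis plan. That would narrow the ambiguity. It would not remove the stated instruction to discard and keep recruiting, or its conflict with the 17-enrolled rule.

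**Conclusion.** The point stands in this form: the rule permits selection on outcome, conflicts with the Sample size section, and leaves type I error dependent on who happens to go missing. Across the assumed patterns above, the error runs from 1.3% (20% of successes lost) to 12.2% (30% of failures lost). It is unchanged at 3.4% when loss is unrelated to outcome, and it exceeds 5% only when failures are lost preferentially. The contradiction between sections and the open-ended number treated rest on the text alone; the error figures rest on the assumed shares. Because the rule governs both the stage 1 decision and the proof-of-concept claim, and the article says recruitment had not begun, it should be corrected before the first child is enrolled.

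**What to change.** - In Methods for additional analyses, delete the discard-and-replace sentences.
- Define the primary set as every child in whom infusion was started, in order of infusion: the first 9 for stage 1 and the first 17 for the final test.
- In the Simon count, treat death, transplant or unknown status at 24 weeks as not surviving with native liver, after using the routine follow-up data that Data collection and management allows.
- Keep all infused children in the safety and tolerability counts. Censor at last contact in the time-to-event summaries, and use available data for each secondary endpoint.
- In Replacement of subjects, limit replacement to children in whom no infusion was started. Without this, a post-treatment replacement route remains.
- Reconcile Sample size, Replacement of subjects, Statistical methods and Methods for additional analyses so that all four use the same denominator.

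The change is to wording only. Its cost is power: about 78%, 75% or 68%, against the planned 80%, if 2%, 5% or 10% of true successes have unknown status. That makes it worth establishing 24-week status for every infused child.
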